#### Tertiary outcomes

Tertiary outcomes include (1) the time to initiation of postoperative activities around the bed, (2) the total volume of chest tube drainage, (3) the time to chest tube removal, (4) the duration of oral analgesic medications taken by the subject postoperatively in the telephone follow-up, and (5) the total amount of oral analgesic medications taken postoperatively. The total volume of chest tube drainage is referred to as the total amount of chest tube drainage until the chest tube removal. The time to initiate postoperative activities around the bed and time to chest tube removal are measured in hours, i.e., the time of the event minus the time of the end of surgery.

#### Safety outcomes

Safety outcomes are assessed separately and then combined for all subjects, consisting of adverse events during and after surgery. The incidence of adverse events after the surgery is tracked up to the 7th postsurgical day (study day 8). Adverse events include postoperative nausea and vomiting (PONV), fever, constipation, dizziness, headache, insomnia, itching, prolonged chest tube leakage, new-onset atrial fibrillation, severe ventricular arrhythmia, deep venous thrombosis, pulmonary embolism, pulmonary atelectasis, cardiac arrest, ileus, urinary retention, chylothorax, pneumothorax, and organ failure. The definitions of adverse events are displayed in the Supplementary Table S1. Any adverse event in relation to the study interventions must be reported to DMC in the form of an “Adverse Event Form” within 24 h. In the event of a serious adverse event, such as an unexpected deterioration in the patient’s clinical condition during the perioperative period, the attending anesthesiologist could require unblinding and adjustment or discontinuation of administration.

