Liposome bupivacaine (LB) is a novel local anesthetic with water-soluble bupivacaine wrapped in a liposome, allowing for a steady, continuous release of the drug for up to 72 to 96 h (12, 13). In 2011, liposomal bupivacaine was approved by the U.S. Food and Drug Administration to be used in single-dose wound infiltration for postsurgical analgesia in adults, and then the indication was expanded to transverse abdominis plane blocks and interscalene brachial plexus blocks (14, 15). Liposome bupivacaine appears safe when used in fascial plane blocks and peripheral nerve blocks (16–20). Whether LB is superior to traditional local anesthetics in postoperative analgesia after thoracic surgery remains controversial. Several retrospective studies have suggested that LB applied in minimally thoracic surgery improved postoperative pain, decreased opioid use, and shortened hospital stay in comparison with bupivacaine hydrochloride (HCl) (21–23). A recent randomized controlled trial including 50 patients undergoing minimally invasive lung surgery indicated that LB for intercostal nerve block provided no benefit in mitigating postoperative pain compared with bupivacaine plus epinephrine (18). However, that study had a smaller sample size and did not exclude the patients with more complex pain problems. To date, the analgesic efficacy of LB used in ESPB procedures on acute or chronic postsurgical pain remains unknown.

In this context, we designed this multicenter randomized controlled trial to determine the effect of LB versus bupivacaine HCl for preoperative ultrasound-guided ESPB on postoperative acute and chronic pain in patients undergoing video-assisted thoracoscopic lung surgery. In addition, we will also evaluate its safety profile when used in the ESPB procedures.

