### Perioperative management

The flow of the participants through this trial is depicted in Figure 1. Subjects do not receive sedative or analgesic medications preoperatively. In the operating room, standard monitoring includes electrocardiography, non-invasive cuff blood pressure, pulse oximetry, and temperature. The left or right radial artery is cannulated following anesthesia induction, and continuous radial artery pressure is measured. General anesthesia is induced with propofol (2–2.5 mg/kg), sufentanil (0.3–0.5 μg/kg), and cisatracurium (0.2 mg/kg) in sequence. Following tracheal intubation with a double-lumen tube, unilateral bronchial ventilation is conducted with a tidal volume of 4–6 mL/kg and a respiratory rate of 12–16 times/min, aiming to maintain the end-tidal carbon dioxide at 35–45 mmHg and pulse oxygen saturation of ≥95%. The location of the bronchial tube is then confirmed using flexible fiberoptic bronchoscopy. Anesthesia is maintained with sevoflurane inhalation targeting a bispectral index value between 40 and 60. Intraoperative analgesia is provided with sufentanil and remifentanil: sufentanil 0.1–0.2 μg/kg is given before incision at the beginning of surgery, and remifentanil (0.05–0.2 μg/kg/min) is infused continuously for intra-operative analgesia. Additional doses of sufentanil can be given intraoperatively if necessary, and sufentanil is added 0.1–0.2 μg/kg when the remifentanil is discontinued at the end of the operation. The additional doses of cisatracurium can be incremented intraoperatively as needed. Intraoperative hypotension (defined as a decrease in mean blood pressure [MBP] of >20% of baseline or MBP of <65 mmHg) would be treated with intravenous ephedrine of 6–10 mg or phenylephrine of 50–100 μg, and bradycardia (defined as heart rate [HR] of <50 beats/min) would be treated with intravenous atropine of 0.3–0.5 mg.

At the end of the surgery, all subjects received ondansetron of 8 mg as an antiemetic after the last stitches. Subjects are transferred to a post-anesthesia care unit (PACU) and kept there for at least 1 h before returning to the thoracic ward. The surgical day is regarded as the study day 1, and the day following surgical day is the study day 2.

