The variations in study protocols and injection site locations could influence study results. The pharmacokinetics profile of liposomal bupivacaine is apparently related to the duration of regional blocks (43). Liposomal bupivacaine exhibits a biphasic model, dose-related release profile with an initial peak release within 1 h of execution related to extra liposomal bupivacaine included in every ampule, followed by a further peak 12 to 48 h later, associated with the release from the liposomes (13, 44). Hence, preemptive analgesia with liposomal bupivacaine has the potential to reduce postoperative pain intensity. Furthermore, the rate of bupivacaine release from liposomes is speculated to be related to the vascularity of the surrounding tissue at the injection site. For example, approximately 30% of bupivacaine is released during the first 24 h when it infiltrates directly into tissues in knee replacement, and approximately 90% in more vascularly distributed hemorrhoidectomy (45). The erector spinae plane does not have a rich vascular plexus, and the rate of bupivacaine release from liposomes may be similar to other fascial plane blocks, allowing for prolonged anesthetic duration. More studies are warranted to determine the exact features and effectiveness of this block in various surgical procedures. To date, this is the first randomized controlled study to determine the efficiency of liposomal bupivacaine for ESPB on postoperative pain in thoracic surgery.

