In this study, we formulate certain rules for NRS scoring to achieve multicenter consistency and eliminate the influence of external factors on pain outcomes. For instance, we have implemented the wWOCF protocol for recording NRS pain intensity scores in the first 72 h after surgery. This method is designed to reduce the influence of opioid rescue medications on the NRS evaluations. Specifically, if patients receive rescue medication within a 2 h “window” before an assessment, we will replace the score for that time point with the highest (“worst”) NRS score recorded before the administration of the initial rescue medication. In addition, we employ a nocturnal recall score to minimize the disruption to the patient’s nighttime rest. We do not take bedside face-to-face scoring at night (23:00 to 06:00, the following day). If the subject is awake within the time window, the subject or companion recollects the pain state the following morning, and if the subject is asleep during the time window, the NRS score is assigned a uniform value of 2.

Our study has several limitations. First, partial subjects were discharged within 72 h after surgery, and NRS scores for these subjects could only be followed up by telephone. Second, adverse events are only tracked up to the 7th postsurgical day without further follow-up. Finally, varying durations of oral analgesic medications or non-protocol analgesics may interfere with the NRS scoring for pain.

In conclusion, this randomized clinical trial was designed to determine the effect of liposomal bupivacaine versus bupivacaine HCl for preoperative ultrasound-guided ESPB on postoperative pain in video-assisted thoracoscopic lung surgery. We expected that liposomal bupivacaine could be safely employed in ESPB, and liposomal bupivacaine for preoperative ultrasound-guided ESPB would be more effective than bupivacaine HCl in reducing the area under the curve of pain scores at rest from 0 to 72 h postoperatively.

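### The prespecified safety outcomes do not name the events most specific to the study drug and the block, although the safety of liposomal bupivacaine in ESPB is a stated aim

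*Protocol article*

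**What the plan says.** The Safety outcomes section of the protocol article describes the outcomes as "consisting of adverse events during and after surgery", with postoperative follow-up to study day 8. It then lists the events: "Adverse events include postoperative nausea and vomiting (PONV), fever, constipation, dizziness, headache, insomnia, itching, prolonged chest tube leakage", continuing with "new-onset atrial fibrillation, severe ventricular arrhythmia, deep venous thrombosis, pulmonary embolism, pulmonary atelectasis, cardiac arrest, ileus, urinary retention, chylothorax, pneumothorax, and organ failure". That makes 8 + 11 = 19 named events. The same 19 appear in the Methods part of the Abstract and in the footnote to Table 1. Definitions are referred to Supplementary Table S1, which is not shown. The section also requires that any adverse event related to the study interventions be reported to the DMC within 24 h.

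Safety is a stated aim. The Introduction says: "In addition, we will also evaluate its safety profile when used in the ESPB procedures". The opening of the Discussion says that adverse events associated with LB in this block will be explored, and its last paragraph says: "We expected that liposomal bupivacaine could be safely employed in ESPB".

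Perioperative management gives numerical definitions of two haemodynamic events. Intraoperative hypotension is a fall in mean blood pressure of more than 20% from baseline, or a value below 65 mmHg. For the other, "bradycardia (defined as heart rate [HR] of <50 beats/min) would be treated with intravenous atropine". Both serve there as triggers for treatment. Neither is among the 19 safety events.

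**The concern.** The arms differ in the local anaesthetic formulation, and both receive the same block. The events most specific to that contrast and procedure are systemic local-anaesthetic toxicity, haemodynamic change after the block, a new neurological deficit and complications at the injection site. The named outcomes include none of these. If the plan is followed as written, the by-arm safety table will omit them. A finding of similar adverse events could then be read as evidence on the safety of LB in ESPB when the most relevant events were not prespecified for systematic comparison.

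Two features of the design add weight. First, Study interventions places the block after induction of anaesthesia, so the patient cannot report early neurological symptoms. Blood pressure and heart rate are then among the main signs that can be observed. Second, the Discussion describes an early release of bupivacaine, "followed by a further peak 12 to 48 h later, associated with the release from the liposomes", while Table 1 marks vital signs in the intra-operative column only.

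**Working it through.** **1. The plan's own figure.** Inputs from Sample size calculation: difference 15, SD 38.7, power 80%, alpha 0.05 (two-sided, from Statistical analysis), dropout 20%.

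- Normal approximation: n = 2 × (1.96 + 0.8416)² × 38.7² / 15² = 104.5, so 105 per arm. The exact t-test needs 106.
- Dropout: 105 / 0.8 gives 132 per arm (264 in total), and 106 / 0.8 gives 133 per arm (266 in total).

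The stated 272 (136 per arm) is within 3% of both totals. The trial is sized on the efficacy AUC, and changing the adverse-event list does not alter the number.

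**2. The list against the missing events.**

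| Event | Named among the 19? | Where else the article touches it |
|---|---|---|
| Suspected systemic local-anaesthetic toxicity | No | Indirectly, through severe ventricular arrhythmia, cardiac arrest, dizziness and headache in the list |
| Hypotension | No | Defined in Perioperative management as a treatment trigger |
| Bradycardia | No | Defined in Perioperative management as a treatment trigger |
| New sensory or motor deficit | No | Not mentioned |
| Block-site haematoma or infection | No | Not mentioned as an outcome; pneumothorax is listed and could follow a block or the surgery |

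**3. What 136 patients per arm can say.** The article gives no event rates, so the rates below are assumptions.

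- Zero events in n patients: one-sided 95% upper limit = 1 − 0.05^(1/n). For n = 136 this is 2.2%. For 108 evaluable patients (136 × 0.8 = 108.8, rounded down) it is 2.7%.
- Chance of at least one event in the LB arm = 1 − (1 − p)^136: 12.7% at p = 0.1%, 49.4% at 0.5%, 74.5% at 1% and 93.6% at 2%.
- Power to show a difference in a commoner event, with 136 per arm and two-sided alpha 0.05: Φ[(|p₁ − p₂| − 1.96 × SE₀) / SE₁], where SE₀ uses the pooled rate and SE₁ the separate rates. This gives 35% for 5% vs 10%, 64% for 10% vs 20%, and 48% for 20% vs 30%.

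Naming the events therefore gives a description by arm. It does not give proof of safety. The 2.2% limit comes from the arm size and stays the same after the list is extended. Even that limit can be claimed only for events that were systematically looked for.

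**The case against.** The strongest reply is that the list is neither closed nor blind to the study drug. The events are introduced as inclusions, not as an exhaustive set. Severe ventricular arrhythmia, cardiac arrest, dizziness and headache could reflect systemic toxicity, and pneumothorax could follow the block. Table 1 ticks adverse events intra-operatively, in the PACU and up to study day 8. A suspected toxic reaction or a block-site haematoma judged related would reach the DMC within 24 h. Supplementary Table S1 and the case report form are not shown, and the intra-operative information row of Table 1 might already hold blood pressure and heart rate events.

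Much of this stands, and it rules out several stronger readings:

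- A reader might infer that the list holds only opioid effects and surgical complications. It does not, as the cardiac items show.
- A reader might infer that the listed events are those least likely to differ between arms. Total rescue opioid is the first secondary outcome, and the Discussion links opioid sparing to less nausea, vomiting and delayed peristalsis, so the opioid-related items are plausible targets of the comparison.
- A reader might take the nominal doses (266 / 100 = 2.66) as a ratio of risk. The article describes slow release that depends on the tissue, so nominal dose is not exposure.

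The reply does not close the gap. Reporting to the DMC depends on a clinician attributing the event to the study treatment, and hypotension under general anaesthesia is easily attributed elsewhere. The Data monitoring committee section describes that body's work as resolving data-collection questions and judging adherence to protocol medication. It does not mention a comparison of event rates. Table S1 is described only as giving definitions.

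**Conclusion.** The point holds in a limited form. The named safety outcomes omit the events most specific to the drug and the block, including two that the protocol already defines, while the safety of LB in ESPB is a stated aim. The consequence is a by-arm safety table without those events. No efficacy analysis and no sample size is affected.

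It would go too far to say that the trial cannot support any safety conclusion, or that it has already drawn one. The closing paragraph of the Discussion states an expectation, and nowhere does the article conclude that one stated dose is as safe as the other. The verdict assumes that Table S1 and the case report form add no further events to the list. If they do, the point reduces to naming those events in the Safety outcomes section. Even with a full list, a toxicity rate below about 2% could not be excluded with 136 patients per arm.

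**What to change.** Add the following to the Safety outcomes section, Table S1 and the case report form, and tabulate them by arm:

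- hypotension and bradycardia by the definitions already in Perioperative management, recorded intraoperatively after the block;
- suspected local-anaesthetic systemic toxicity;
- new sensory or motor deficit;
- block-site haematoma or infection.

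The haemodynamic items are confined to the intraoperative period because that is where the article defines them and where Table 1 schedules vital signs. The other items run through study day 8, matching the existing follow-up.

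If the list is not extended, limit the safety statement to the listed events. In either case, report that rare toxicity (below about 2% with 136 per arm) cannot be excluded.

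The cost is an amendment to the case report form and Table S1. Recruitment has started, so neurological or block-site events may not be recoverable for patients already enrolled. The report should say from what date each item was collected. No change to dose or clinical management is proposed.

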### Sample size calculation

Between January 2023 and March 2023, we conducted a prospective study on two groups of 10 patients each. All participants underwent video-assisted thoracoscopic lung surgery and were administered a preoperative ultrasound-guided ESPB, with one group receiving liposome bupivacaine and the other bupivacaine HCl. The results showed that the postoperative AUC NRS-R0-72 was 247 ± 35 in the LB group versus 262 ± 43 in the BUPI group. Based on the preliminary study, the sample size was determined to ensure the ability to detect a mean difference of 15 in the primary efficacy outcome, and we suggest that this difference is clinically relevant. This calculation is performed with a two-group *t*-test, a standard deviation of 38.7, an 80% power, and a 0.05 level of significance. Considering a 20% dropout rate, this study will enroll a total of 272 patients, with 136 in each group. The sample size is calculated using the SAS software (version 9.4, SAS Institute Inc).

### Statistical analysis

Baseline characteristics will be tabulated using applicable summary statistics. Outcome data will be analyzed according to the intention to treat (ITT) principle and secondarily with the per-protocol (PP) analysis.

The ITT population will comprise all randomized patients who receive ultrasound-guided ESPB procedures and complete the surgery with the primary outcome measurement available. These subjects will be analyzed according to the groups to which they are randomized, regardless of whether the surgical procedure is converted to an open thoracotomy or any other surgical procedure implemented within 3 months postoperatively. Subjects who are given non-protocol pain medication postoperatively will also be included in the ITT analysis. Subjects whose consent is withdrawn will have their data retained until the time of withdrawal. The PP population will comprise those patients who complete the study based on the original protocol. Subjects with modifications of the original surgical approach to open thoracotomy or who undergo any other surgical procedures within 3 months after surgery are specifically excluded from this analysis. Data from subjects whose consent is withdrawn will be used until the time of withdrawal of consent.

Demographic information and baseline characteristics will be described using descriptive statistics only, with no between-group comparisons. Continuous data will be displayed as means and standard deviations or medians and interquartile ranges, depending on data distribution. Categorical data will be summarized as counts and percentages. Between-group differences of continuous data will be analyzed using the independent t-test or Mann–Whitney rank sum test as appropriate, while categorical data will be analyzed using the Chi-squared test or Fisher’s exact test as appropriate. To analyze the treatment effect, odds ratios are calculated for binary data and mean differences for continuous data, each together with their 95% confidence intervals. For the primary outcomes, the between-group difference of AUC NRS-R_0-72_ is regarded as significant at the two-side *p*-value of 0.05. For the secondary and tertiary outcomes, multiple comparisons are adjusted for the significance level of probability values by computing the false discovery rate using the Benjamini-Hochberg method. To further understand the cumulative effect of study interventions on postsurgical pain, *post-hoc* analysis is conducted, including AUC NRS-R_0-24_, AUC NRS-R_24-48_, AUC NRS-R_48-72_, AUC NRS-A_0-24_, AUC NRS-A_24-48_, and AUC NRS-A_48-72_, the cumulative amount of opioid rescue analgesics during 0–24, 24–48, and 48––72 h, and the proportion of subjects who are pain-free (NRS-R score of 0 or 1) at 1, 6, 24, 48, and 72 h. To address the missing NRS pain intensity scores during the postoperative 0–72 h, interpolation is performed using one of the following methods: (1) by last observation carried forward (LOCF) imputation method if missing data are located after the last non-missing score, (2) by linear interpolation if more than one missing data occur and are located between two non-missing scores (25). All data will be analyzed using the SAS software (version 9.4, SAS Institute Inc) by an independent statistician.

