## Discussion

This multicenter, randomized, double-blind, parallel-controlled trial will include 272 subjects who will undergo elective video-assisted thoracoscopic lung surgery. We will determine the effect of LB versus bupivacaine HCl for preoperative ultrasound-guided ESPB on AUC NRS-R_0-72_, the amount of opioid rescue analgesics after surgery, time to the first rescue analgesia, AUC NRS-A_0-72_, NRS scores at rest and on activity at different time points during the 0–72 h postoperative period, and NRS scores on activity on postsurgical day 14 and postsurgical 3 months. Our primary hypothesis is that the use of LB for ultrasound-guided ESPB preemptive analgesia provides a lower area under the curve of pain scores at rest 0–72 h postoperatively compared to bupivacaine HCl. Moreover, we will explore the adverse events associated with the application of LB for ultrasound-guided ESPB. The administration of this trial and the presentation of results will follow the Consolidated Standards of Reporting Trials guidelines.

Regional nerve block maneuvers before skin incisions are considered an optimal method of preemptive analgesia, which facilitates the reduction of postsurgical pain. ESPB is a novel interfascial regional anesthesia technique first introduced by Forero et al. in 2016 for thoracic neuropathic pain treatment and has rapidly gained prevalence in a diverse range of surgical procedures (7, 26). In particular, it is easy to implement owing to the simple identification of anatomic landmarks on ultrasound and the fact that no vital organs are nearby (27). Anatomical and radiological investigations in fresh cadavers have suggested that the clinical effects of ESPB are likely derived from the theoretical anterior distribution of the local anesthetics through the intertransverse connective tissue or the costotransverse foramen to infiltrate the ventral crus of the spinal nerves, the dorsal root ganglion, and the sympathetic chain, thereby resulting in an effect similar to epidural analgesia (7, 28).

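### The odds ratio is the only planned effect measure for adverse events; it fails when the bupivacaine HCl arm has no events and cannot show what excess risk the expected safety statement rules out

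*Protocol article*

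**What the plan says.** All references are to the protocol article.

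- **Aim.** The Introduction says of LB: "In addition, we will also evaluate its safety profile when used in the ESPB procedures". The Discussion calls this exploration: "Moreover, we will explore the adverse events associated with the application of LB for ultrasound-guided ESPB". Its closing paragraph then states an expectation: "We expected that liposomal bupivacaine could be safely employed in ESPB".
- **Outcomes.** Safety outcomes lists 19 event types, from nausea and vomiting to cardiac arrest, pulmonary embolism and organ failure, and says: "Safety outcomes are assessed separately and then combined for all subjects, consisting of adverse events during and after surgery".
- **Analysis.** Statistical analysis gives general rules by data type. "Categorical data will be summarized as counts and percentages". For comparison, "categorical data will be analyzed using the Chi-squared test or Fisher’s exact test as appropriate", and for the size of the effect, "odds ratios are calculated for binary data and mean differences for continuous data, each together with their 95% confidence intervals". Adverse events have no separate rule, so these apply to them.
- **Size.** Sample size calculation rests on a difference of 15 in the resting-pain area under the curve. It contains no safety quantity.

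**The concern.** The trial has a safety aim and an expected safety statement. The useful question for such a statement is how large an excess of harm with LB the data still allow. The stated measure does not answer it. An odds ratio carries no absolute risk, and for the rarest and gravest listed events there will often be no usable estimate because the comparator arm has none.

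The remaining between-group tool is a test for a difference in a trial sized for pain. A non-significant result would be the likely outcome even under a sizeable excess of a rare event. At stake is a closing statement on safe use that rests on little more than the absence of a significant difference.

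**Working it through.** **1. The plan's own figure.** Inputs from Sample size calculation: difference 15, SD 38.7, power 80%, alpha 0.05 (taken as two-sided), dropout 20%. The two-sample t-test needs 106 per arm (power 80.2%; 105 gives 79.8%). Then 106/0.8 = 132.5, so 133 per arm and 266 in total. The stated 272 (136 per arm) is within 3% of this. The number is explained by pain alone, and no adverse event rate enters it.

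**2. When the odds ratio has no finite value.** With LB in the numerator, the odds ratio is infinite if only BUPI has no events and undefined if neither arm has any. Both cases require zero events in BUPI, with probability (1 − p)^136. The article gives no event rates, so p is an assumption:

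| Assumed true rate p | P(no BUPI events), 136 per arm |
|---|---|
| 0.2% | 0.998^136 = 76% |
| 0.5% | 0.995^136 = 51% |
| 1% | 0.99^136 = 25% |

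If only LB has no events, the odds ratio is 0, which is finite; for 0 v 3 the exact upper 95% limit is 2.41.

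**3. What a non-significant test would mean.** Fisher's exact test, 136 per arm, LB v BUPI: 5 v 0 gives p = 0.060 and 6 v 0 gives p = 0.030. So five events against none would count as no significant difference.

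Miss rates were found by exact enumeration of two binomials at two-sided 0.05. Fisher was used when an expected count was below 5 and uncorrected chi-squared otherwise; a detection means p < 0.05 with the higher rate in LB. All rates are assumptions.

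| BUPI v LB | Missed, 136 per arm | Missed, 109 per arm (136 × 0.8) |
|---|---|---|
| 1% v 5% | 62% | 76% |
| 5% v 10% | 65% | 71% |
| 10% v 20% | 36% | 45% |

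For 1% v 5% at 136 per arm, the miss rate is 66% if Fisher is always used and 51% if chi-squared always is. Larger excesses in common events are detectable: 10% v 22.5% has about 80% power.

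**4. What a risk difference would show instead.** The Newcombe interval combines the Wilson limits (l, u) of each arm. With d = p1 − p2, the lower limit is d − √[(p1 − l1)² + (u2 − p2)²] and the upper limit is d + √[(u1 − p1)² + (p2 − l2)²]. Arm 1 is LB. For 0/136 the Wilson limits are 0 and 2.75%; for 3/136 they are 0.75% and 6.28%.

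For 3 v 0, d = 3/136 = 2.21%:
- lower = 2.21 − √[(2.21 − 0.75)² + 2.75²] = −0.9%
- upper = 2.21 + √[(6.28 − 2.21)² + 0²] = 6.3%

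| Events, LB v BUPI | Odds ratio (exact 95% CI) | Risk difference (Newcombe 95% CI) |
|---|---|---|
| 0 v 0 | undefined | 0% (−2.7% to 2.7%) |
| 3 v 0 | infinite (0.42 to infinity) | 2.2% (−0.9% to 6.3%) |

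For 3 v 0, the odds-ratio interval has no upper bound, while the risk difference says that an excess above 6.3 percentage points is excluded. For 0 v 0, only the risk difference says anything.

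**The case against.** The strongest case on the other side is that safety here is exploratory, that the only primary hypothesis concerns pain, and that sizing on pain fits those aims. Counts and percentages per arm are planned, so any reader would see 5 v 0 and could compute a risk difference. The safety wording is one sentence of expectation in the Discussion, and the same section supports it with earlier literature. Low power for rare events is inherent in 272 patients, and no choice of measure changes it. Zero-cell conventions may also stand in an analysis plan that is not shown.

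Much of this stands, and it rules out several stronger readings:

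- *The plan treats p > 0.05 as proof of safety.* No section says so.
- *A non-inferiority margin is missing.* An exploratory aim does not need one.
- *The odds ratio has no finite value whenever either arm is empty.* The chance that at least one arm has no events is 76% at a 0.5% rate and about 44% at 1%, but this includes the case of LB alone having none, where the odds ratio is 0. The figures that apply are 51% and 25%.
- *The combined rate would hide a rise in serious events behind fewer opioid-related ones.* Safety outcomes has each event assessed separately before combination. The Discussion's link between opioid sparing and fewer side effects concerns the block itself, which both arms receive.
- *Most relevant harms would be missed.* That depends on rates which the article does not give.

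What the objection does not remove is the choice of effect measure. The article states it, so it is not a detail left to another document. Nor do counts replace an interval: they do not say what excess remains possible.

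**Conclusion.** The point holds as a matter of method and wording. The stated effect measure for binary data is infinite or undefined with probability of about 51% at a true BUPI rate of 0.5% (76% at 0.2%, 25% at 1%). At no rate does it give the absolute excess that a safety statement needs. The difference tests cannot fill the gap: an assumed 1% v 5% is missed about 62% of the time with 136 per arm. The probabilities rest on assumed rates; the behaviour of the odds ratio with no BUPI events and the p-value for 5 v 0 do not. The change is worth making because it costs little and lets the trial address its own safety aim. The pain analysis and the sample size are unaffected.

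**What to change.** 1. In Statistical analysis, add for adverse events: the main between-group measure is the risk difference (LB minus BUPI) with a 95% confidence interval by a method defined for zero cells, such as Newcombe's. The odds ratio may stay as a supplement where it can be estimated.
2. In the same place, state that the interval describes safety and that a non-significant chi-squared or Fisher test will not be read as evidence of it. The two can disagree: 5 v 0 gives an interval of 0.2% to 8.3%, which excludes zero, beside p = 0.060. Naming the interval as the main summary settles this in advance.
3. In the closing paragraph of the Discussion and in the final report, limit the safety statement to the excess risk that the interval excludes.
4. Optionally, show serious events as a group separate from minor ones, next to the combined rate.

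**Cost.** A few sentences and one table column, with no new data or patients. The safety statement becomes more modest: even with no events in either arm, an excess of up to 2.7 percentage points is not excluded. Study design and status says the database stays locked until the final analysis, so the change can be fixed before then.
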